## Abstract

**Background:**

We have developed a new paradigm that targets the recognition of facial expression of emotions. Here we report the protocol of a randomised controlled trial of the effects of emotion recognition training on mood in a sample of individuals with depressive symptoms over a 6-week follow-up period.

**Methods/Design:**

We will recruit 190 adults from the general population who report high levels of depressive symptoms (defined as a score ≥ 14 on the Beck Depression Inventory-II). Participants will attend a screening session and will be randomised to intervention or control procedures, repeated five times over consecutive days (Monday to Friday). A follow-up session will take place at end-of -treatment, 2-weeks and 6-weeks after training. Our primary study outcome will be depressive symptoms, Beck Depression Inventory- II (rated over the past two weeks). Our secondary outcomes are: depressive symptoms, Hamilton Rating Scale for Depression; anxiety symptoms, Beck Anxiety Inventory (rated over the past month); positive affect, Positive and Negative Affect Schedule (rated as ‘how you feel right now’); negative affect, Positive and Negative Affect Schedule (rated as ‘how you feel right now’); emotion sensitivity, Emotion Recognition Task (test phase); approach motivation and persistence, the Fishing Game; and depressive interpretation bias, Scrambled Sentences Test.

**Discussion:**

This study is of a novel cognitive bias modification technique that targets biases in emotional processing characteristic of depression, and can be delivered automatically via computer, Internet or Smartphone. It therefore has potential to be a valuable cost-effective adjunctive treatment for depression which may be used together with more traditional psychotherapy, cognitive-behavioural therapy and pharmacotherapy.

**Trial registration:**

Current Controlled Trials: ISRCTN17767674

## Background

Mood disorders are highly prevalent in the general population, dominated by major depression, and constitute a substantial burden of disease. At present, National Institute for Clinical Excellence guidelines recommend psychotherapy for mild depression, and cognitive-behavioural therapy (CBT) for moderate depression [1], but these therapies require individual intervention and therefore, while cost-effective, are expensive. Here we propose a study to investigate the potential of a novel cognitive bias modification technique for reducing negative mood and improving positive mood in an analogue population of those with high levels of depression symptoms. This targets biases in emotional processing characteristic of depression, and can be delivered automatically via computer, Internet or Smartphone. Computerised programs for CBT have already been shown to improve accessibility to treatment and reduce symptoms of depression [2]. Their aim is to deliver existing talking-therapy CBT techniques via computer. An alternative emerging option is to use the computer to deliver novel techniques, which like CBT aim to alter biasing in thinking styles but do so in a rather different manner.

Cognitive-bias modification (CBM) encompasses a range of techniques designed to manipulate biases in cognitive processing characteristic of specific psychopathologies and involved in the maintenance of the disorder [3]. For example, attentional bias towards threat is a feature of anxiety disorders, and can be reduced through retraining procedures [4]. There have been innovations in CBM for a range of biases, including attention, interpretation, and memory. However, a key feature of emotion processing highly relevant to psychopathology has received little attention to date – the recognition of facial expression of emotions. Faces play a key role in everyday life, and the accurate recognition of emotional content in faces is critical to social functioning. This is disrupted in a range of psychiatric disorders – for example, people with depression show a negative bias whereby they fail to identify happiness in faces [5,6]. In particular, the negative bias characteristic of depression also predicts relapse in currently depressed and remitted patients [7]. This strongly suggests that such biases play a causal role in the aetiology and maintenance of depression. Indeed, recent advances in the CBM of depression have focused on promoting positive biases rather than merely reducing negative biases [8,9]. We have developed a new paradigm that targets the recognition of facial expression of emotions by initially assessing the threshold for detecting one emotion over another in an ambiguous expression (for example, a blend of happiness and sadness), and then providing feedback to shift this threshold (for example, to favour identification of happiness over sadness). Training consists of feedback to shift the participant’s balance point, estimated by presenting exemplar faces from a 15-frame morphed face image continuum using a two-alternative forced choice procedure. In the training condition, the ‘correct’ classification shifted two morph steps towards ‘happy’; the two images nearest the balance point that the participant would have previously classified as ‘sad’ at baseline were considered ‘happy’ in terms of providing feedback. Feedback in the control condition was based directly on baseline performance (Figure 1).

**Figure 1 F1:**
[figure not shown]
Sample of face morph sequence.

Preliminary results from adults recruited from the general population on the basis of high levels of depressive symptoms on the Beck Depression Inventory-II (BDI-II) show that this manipulation of the perception of emotion in ambiguous facial expressions, designed to promote the perception of positive emotion over negative emotion, may have therapeutic benefit that persists for at least two weeks [10]. The strength of the observed effect of training on positive mood appears to strengthen over time. This is consistent with recent models of the action of antidepressant medication, which suggest that drug treatment has early effects on emotional processing bias including the ability to detect positive versus negative facial expressions [11]. This is argued to result in therapeutic benefit (i.e., improved mood) only after sufficient time has elapsed to allow interaction with others, where alteration in these processing biases gives rise to more positive social interactions. Our intervention aims to target these biases directly through automated behavioural feedback. Here we propose taking the next critical step to translate this work to establish the therapeutic potential of this novel approach.

### Study objectives and hypotheses

The present project aims to establish the effects of emotion recognition training on mood in a sample of individuals with depressive symptoms over a 6-week follow-up period. Preliminary evidence suggests a beneficial effect of emotion recognition training on positive mood at 2-week follow-up following four consecutive days of training [10]. However, we would hypothesise that these effects would strengthen over time, by modifying the nature of social interaction through the perception of positive emotion over negative emotion. We will therefore investigate the longer-term effects of training over time, using a 6-week follow-up period. We hypothesise that individuals randomised to receive an intervention designed to modify emotion perception designed to increase the perception of happiness over sadness in ambiguous expressions will show reduced depressive symptoms, reduced negative affect, and increased positive effect, compared with individuals randomised to receive a placebo intervention.

## Methods/design

### Design

This study will examine the effects of emotion recognition training on a sample of individuals with depressive symptoms over a 6-week follow-up period. Participants will attend a screening session and will be randomised to intervention or control procedures, repeated five times over consecutive days (Monday to Friday). A follow-up session will take place at end-of-treatment, 2-weeks and 6-weeks after training.

### Participants and recruitment

We will recruit 190 adults from the general population who report depressive symptoms (defined as a score ≥ 14 on the BDI-II [12]). A score ≥ 14 is the standard cutoff value used to indicate mild depression, as described in the BDI-II scoring manual.

A CONSORT diagram of participant recruitment is shown in Figure 2. Participants will be recruited from the staff and students at the University of Bristol and the general population. Participants will be recruited by existing email lists, by poster and flyer advertisements, and by word of mouth. They will be asked to contact the research coordinator for further details of the study if they are interested in taking part. Those who meet the study inclusion criteria will be sent the information sheet, and asked to contact the research coordinator again if they would like to sign up for the study or if they require further information. On completion of the study session, participants will be reimbursed £60 for their time and expenses.

**Figure 2 F2:**
[figure not shown]
CONSORT flow diagram.

### Inclusion criteria

For inclusion, participants should: be aged between 18 and 40 years; score ≥ 14 on the BDI-II; have English as their first language or an equivalent level of fluency; and be able to give informed consent as judged by the lead researcher.

### Exclusion criteria

Criteria for exclusion are as follows: primary anxiety disorder, psychosis, bipolar disorder, or substance dependence (other than nicotine and caffeine) as defined by the Diagnostic and Statistical Manual of Mental Disorders, fourth edition; current use of an illicit drug (except cannabis); being at clinically significant risk for suicidal behaviour; use of psychotropic medication in the last 5 weeks prior to the study; major somatic or neurological disorders and concurrent medication that could alter emotional processing (including active treatment with counselling, cognitive behavioural therapy, or other psychotherapies) – we will allow intermittent use of medication, judged by the principal investigator; and participants who in the opinion of the lead researcher are not appropriate for participation. Participants who develop or engage in any of these criteria during the course of the study will be removed from the final analysis.

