### Sample size determination

Our preliminary data indicate an effect size of *d* = 0.43 at 2-week follow-up, corresponding to a difference of 3 points on the Positive and Negative Affect Schedule (PANAS). This indicates that a sample size of *n* = 172 will be required to achieve 80% power at an alpha level of 5%. This effect size may be conservative as our data indicate a trend for the effect of training to strengthen over time, which is consistent with our underlying theoretical model. This sample size will give us equivalent power to detect a difference of 5 points on the BDI-II. We will therefore recruit *n* = 190 participants, including 10% over-recruitment to accommodate potential attrition.

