### Randomisation

Participants will be randomised to intervention or control procedures, repeated five times over consecutive days (Monday to Friday). Equal numbers of participants per group will be maintained (i.e., 95 intervention and 95 control). In advance of the study, an experimental collaborator (who will have no direct contact with the study participants) will prepare a numeric code using random number assignment software. Once a participant has passed the screening assessments, the lead researcher will contact the experimental collaborator who will provide treatment group allocation.

The lead researcher will enter the treatment group code into the computer and will not be present in the room while the participant completes the computer procedures to ensure that blinding is maintained.

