Mood assessments (BDI-II, Beck Anxiety Inventory, Hamilton Rating Scale for Depression and PANAS) will be taken at baseline, at the end of treatment, and at 2-week and 6-week follow-up. Behavioural assessments (Emotion Recognition Task, Scrambled Sentences Test, and the Fishing Game) will be taken at the end of treatment, and at 2-week and 6-week follow-up. 6-week follow-up will also include a visual analogue scale rating of how helpful the participant thought the experimenter was, to ensure that there are no differences between treatment groups which may affect blinding. At 6-week follow-up will we reassess the initial exclusion criteria, to establish any change in these (Table 3).

**Table 3 T3:** Timings of procedures of follow-up sessions (end of treatment, 2 weeks and 6 weeks)

**Time (minutes post arrival)**	**Task**
0	Mood assessments and behavioural tasks
20	Exclusion criteria (6-week only)
30	Visual analogue scale rating of experimenter (6-week only)
40	Depart

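### Randomised participants who later meet an exclusion criterion are dropped from the final analysis, which can bias the primary BDI-II comparison and discards available outcomes

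*Protocol article*

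**What the plan says.** After listing the exclusion criteria, the protocol article (Exclusion criteria) sets an analysis-set rule: "Participants who develop or engage in any of these criteria during the course of the study will be removed from the final analysis". The list includes "being at clinically significant risk for suicidal behaviour", concurrent medication that could alter emotional processing, "including active treatment with counselling, cognitive behavioural therapy, or other psychotherapies", and a discretionary item, "participants who in the opinion of the lead researcher are not appropriate for participation".

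Randomisation gives the order of events: "Once a participant has passed the screening assessments, the lead researcher will contact the experimental collaborator who will provide treatment group allocation". A criterion first met later in the study is therefore met after allocation. Procedures adds: "At 6-week follow-up will we reassess the initial exclusion criteria, to establish any change in these". The Statistical plan sets the primary analysis at that same time point: a linear regression for 6-week mood with BDI-II as primary outcome, adjusted for baseline mood and other covariates.

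Nothing in the article limits the removal rule to a secondary analysis, and nothing states that the primary analysis keeps everyone as randomised. The sample size section allows for losses only by "including 10% over-recruitment to accommodate potential attrition".

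**The concern.** Randomisation makes the arms comparable at allocation. Deleting people for what happens afterwards keeps them comparable only if the deletion is unrelated to outcome, or acts identically on both arms. Here participants enter because of depressive symptoms and are followed for change in those symptoms. Becoming a suicide risk, or starting medication or therapy, plausibly marks a worse course. The trial also hypothesises that training reduces depressive symptoms. If it does, fewer trained participants should meet these triggers, and the rule would remove more poor outcomes from control than from training.

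Two results are then at risk. A real benefit can be understated, because the worst control outcomes are missing. If removal differs between arms for some other reason, a difference can appear where none exists. In both cases 6-week BDI-II scores already collected would be thrown away. This is a stated rule, not a detail left to an analysis plan; an analysis plan that kept these participants would contradict it.

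**Working it through.** **Inputs from the protocol article.** d = 0.43; a 5-point BDI-II difference said to have equivalent power; 172 required for 80% power at 5%; 190 recruited, 95 per arm. Implied BDI-II SD: 5 / 0.43 = 11.6.

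**The plan's own figure.** A two-sided two-sample t-test at d = 0.43 needs 85.87 per arm, so 86 per arm and 172 in total. Then 172 × 1.10 = 189.2, rounded up to 190. The sample size reproduces.

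**Inputs that must be assumed.** The documents give no removal rate and no link between removal and BDI-II. Removal probability was modelled as P(removed) = expit(a + b·Y), with Y the 6-week BDI-II score, the same rule in both arms, and a chosen to give the stated control-arm rate. The estimate is the difference in means among those kept.

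**True benefit of 5 points, SD 11.6**

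| Removal odds ratio per SD | Control removed | Training removed | Estimate | Attenuation |
|---|---|---|---|---|
| 1.5 | 5% | 4.2% | 4.96 | about 1% |
| 2 | 10% | 7.7% | 4.82 | about 4% |
| 3 | 10% | 6.8% | 4.65 | about 7% |
| 3 | 20% | 14.3% | 4.42 | about 12% |

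A second set assumed a residual SD of 9.5 after baseline adjustment (not a figure in the documents), control removal of 5% to 15%, and removal log-odds rising 0.10 to 0.20 per BDI-II point. Estimates ran from about 4.8 to 4.2, a loss of about 3% to 16%. The 16% end needs strong dependence: 0.20 × 9.5 = 1.9 on the log scale, an odds ratio of about 6.7 per SD.

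**No true effect, unequal removal, SD 11.6**

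| Removal odds ratio per SD | Removed, by arm | Spurious difference | Two-sided type I error |
|---|---|---|---|
| 2 | 10% v 5% | about 0.4 points | about 5.5% |
| 3 | 10% v 5% | about 0.5 points | about 6% |
| 2 | 15% v 5% | about 0.7 points | about 7% |
| 3 | 15% v 5% | about 1.1 points | about 9.5% |

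The arm that loses more high scorers looks better, so the sign depends on which arm that is. With equal removal and no treatment effect there is no bias: a separate simulation with 10% removed from each arm gave a type I error of 5.2%.

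**Power at d = 0.43 (t-test, before any bias)**

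| Analysed | Power |
|---|---|
| 190 | 84% |
| 172 | 80% |
| 162 | 78% |
| 153 | 75% |

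The margin is 190 − 172 = 18 participants, shared between attrition and removals. For scale, 10% attrition leaves 171, and removing a further 10% of those leaves about 153.

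**The case against.** The best defence is that the study is an analogue trial, chosen partly to avoid confounding by medication (Discussion), so an analysis free of other treatments has a purpose. That is a reason to report such an analysis. It does not make the comparison unbiased, nor make it the right primary one.

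Five stronger readings are tempting, and the documents do not support them.

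- *The rule certainly biases the result.* It does so only if removal depends on prognosis and also differs between arms or is affected by training. The trial's hypothesis makes this plausible, not certain.
- *Most of the criteria are markers of mood.* The list also contains psychosis, bipolar disorder, substance dependence, illicit drug use and somatic or neurological disease. The psychotropic item is worded as "use of psychotropic medication in the last 5 weeks prior to the study", which read literally cannot begin after allocation; new use would come in through the concurrent-medication item, and intermittent use is allowed. The argument rests on several triggers, not on most.
- *Removal is decided only at 6 weeks, so it reaches only those who attend.* That visit is the only scheduled reassessment described, but the rule covers the whole study. A non-attender would in any case have no 6-week score for the regression.
- *The discretionary item lets an unblinded person choose the analysis set.* The Randomisation section uses a coded allocation and keeps the lead researcher out of the room to preserve blinding. The item also reads as an entry judgement and sits awkwardly with something that a participant develops. It remains undesirable for such a judgement to govern who is analysed, but no imbalance can be presumed from it.
- *The planned 80% power is lost.* This needs attrition and removals together to exceed 18. Baseline adjustment may also recover power: at the assumed residual SD of 9.5, d = 5 / 9.5 = 0.53, and 153 analysed would give about 90%.

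It also stands that every bias figure is an assumption, that expected bias under a real effect is modest and towards the null, and that the documents give no reason to expect unequal removal when training has no effect.

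**Conclusion.** The point holds as a defect in the stated analysis set. The article removes randomised participants from the final analysis for later events, some of which plausibly depend on the outcome and, on the trial's hypothesis, on the arm. Under the assumptions shown, a real 5-point benefit would be understated by about 1% to 16%. If there is no effect but removal is unequal, the spurious difference is about 0.4 to 1.1 points in either direction, with type I error of about 5.5% to 9.5% (at SD 11.6). These are illustrations, not predictions. Reduced power is a secondary and conditional matter. The rule should still be changed, because it governs the primary result, its bias cannot be sized or signed beforehand, and it discards outcome data for no statistical gain.

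**What to change.** Replace the removal sentence in Exclusion criteria with wording such as: *The primary analysis includes all randomised participants in the group to which they were allocated, using every available 6-week BDI-II score, whatever criterion is met after randomisation.* Keep the 6-week reassessment, and use it to report the number and type of criterion events by arm. Present the analysis without these participants only as a labelled sensitivity analysis.

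This changes the analysis set alone, not how any participant is managed. It needs no further data and no larger sample: with all 190 analysed, power at d = 0.43 is 84%. The Trial status section reports one participant recruited at submission, so the change could have applied to the whole trial from that point. It does not solve missing 6-week scores from non-attenders, which is a separate matter. The price is that the estimate includes the effect of any other treatment started during follow-up; the event counts by arm let a reader judge how much that matters.

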### Ethical considerations and informed consent

Ethics approval from the Faculty of Science Ethics Committee has been granted. The study will be conducted according to the revised Declaration of Helsinki and Good Clinical Practice guidelines. The investigator or co-investigator will explain the nature, purpose, and risks of the study to the participant. The participant will receive the information sheet. There will be no time restriction on how long participants take to respond, with the exception that participants who respond after all study places have been filled will not be offered a place on the study. Therefore, participants will be given sufficient time to read the information and consider any implications, and to raise any questions with the investigators prior to making a decision to participate. Participants will be informed that they are free to withdraw at any time.

### Sample size determination

Our preliminary data indicate an effect size of *d* = 0.43 at 2-week follow-up, corresponding to a difference of 3 points on the Positive and Negative Affect Schedule (PANAS). This indicates that a sample size of *n* = 172 will be required to achieve 80% power at an alpha level of 5%. This effect size may be conservative as our data indicate a trend for the effect of training to strengthen over time, which is consistent with our underlying theoretical model. This sample size will give us equivalent power to detect a difference of 5 points on the BDI-II. We will therefore recruit *n* = 190 participants, including 10% over-recruitment to accommodate potential attrition.

### Randomisation

Participants will be randomised to intervention or control procedures, repeated five times over consecutive days (Monday to Friday). Equal numbers of participants per group will be maintained (i.e., 95 intervention and 95 control). In advance of the study, an experimental collaborator (who will have no direct contact with the study participants) will prepare a numeric code using random number assignment software. Once a participant has passed the screening assessments, the lead researcher will contact the experimental collaborator who will provide treatment group allocation.

The lead researcher will enter the treatment group code into the computer and will not be present in the room while the participant completes the computer procedures to ensure that blinding is maintained.

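### The lead researcher is handed the allocation and types in a group code; being out of the room does not blind someone who already holds it

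*Protocol article*

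**What the plan says.** The Randomisation section separates the list from the participants at the start: "an experimental collaborator (who will have no direct contact with the study participants) will prepare a numeric code using random number assignment software". After a participant passes screening, "the lead researcher will contact the experimental collaborator who will provide treatment group allocation". The next step reads: "The lead researcher will enter the treatment group code into the computer and will not be present in the room". The stated reason for this absence, which lasts while the participant does the computer tasks, is to keep the blinding intact. No other blinding safeguard is stated.

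The lead researcher also makes judgements about participants. Under Inclusion criteria, a participant must "be able to give informed consent as judged by the lead researcher". Under Exclusion criteria, one ground is "participants who in the opinion of the lead researcher are not appropriate for participation". The same section carries the criteria past randomisation: "Participants who develop or engage in any of these criteria during the course of the study will be removed from the final analysis". Procedures and Table 3 schedule a reassessment of the exclusion criteria at the 6-week visit.

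Table 1 (day 1) lists screening at minute 15, baseline measures at 40, mood assessments at 50 and computerised training at 60. Procedures adds a check at 6 weeks, a "visual analogue scale rating of how helpful the participant thought the experimenter was", intended to detect differences between groups that might affect blinding.

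**The concern.** The protocol states a way of maintaining blinding, and as worded that way cannot achieve it for the person concerned. The separation gained by giving the list to a no-contact collaborator is lost when the allocation goes to the lead researcher, who has a discretionary role in who counts as a valid participant.

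Two things are at stake. The first is the set of participants analysed. A judgement-based criterion can remove a randomised participant after the person whose opinion defines it has received the allocation, and this touches every outcome, including the primary BDI-II. The second is any outcome scored by study staff. The Hamilton scale is a secondary outcome and would be open to influence if a staff member who knows the allocation rates it.

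A smaller matter is timing. Baseline mood is an adjustment covariate in the Statistical plan, so it should be recorded before anyone at the visit can know the arm.

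**Working it through.** No calculation applies: the protocol gives no figure on this point, and nothing in it would allow the bias to be sized. The check sets the sections side by side.

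**1. What absence from the room does under each reading of the code.** The Randomisation section speaks of a numeric code, of allocation being provided, and of a treatment group code. It does not say which of these readings applies.

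| Reading | What the lead researcher knows | Effect of leaving the room |
|---|---|---|
| The code or message reveals the arm | The arm of every participant | Limits cueing and sight of feedback; does not blind |
| Opaque label shared within an arm | Which participants belong together, but not which set is which | Protects against learning the key from the screen; the two sets of 95 stay visible |
| Opaque code unique to each participant | Nothing about grouping | Adequate; a disclosure concerns one participant |

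Under the second reading, learning the meaning of one label would identify both sets, that is 95 + 95 = 190 participants. Under the third it would identify one. These are conditional statements, because the protocol does not say which reading is meant.

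**2. Which judgements come before the allocation and which after.**

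| Step | Source | Relative to allocation |
|---|---|---|
| Capacity to consent and discretionary exclusion at entry | Inclusion and Exclusion criteria | Before: allocation follows passing screening |
| Baseline mood, minute 50 | Table 1 | Not fixed: may come before or after |
| Training, minute 60 | Table 1 | After: the code is needed here |
| Follow-up mood assessments, including the Hamilton scale | Procedures, Table 3 | After; rater not named |
| Reassessment of exclusion criteria at 6 weeks | Procedures, Table 3 | After; assessor not named |
| Removal from the analysis | Exclusion criteria | After; one ground is the lead researcher's opinion |

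Entry is therefore not exposed. The post-randomisation removals are, and staff-rated outcomes may be. Table 3 also places the 6-week mood assessments (minute 0) before the reassessment of exclusion criteria (minute 20), so the outcome has already been collected when removal is considered.

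**3. Baseline timing.** Passing screening is the earliest point at which the lead researcher may ask for the allocation. Table 1 puts screening at minute 15 and mood assessments at minute 50, while the code is needed only at minute 60. Nothing requires the request to wait until after minute 50, and nothing requires it to come before.

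**4. The blinding check.** A helpfulness rating can show whether the experimenter's manner differed between groups. Equal ratings would not show that the allocation was unknown.

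**The case against.** The strongest reply is that this is a condensed article and that the sensible reading is a masked code. A collaborator without participant contact prepares a numeric code, the lead researcher enters it without knowing its meaning, and then leaves so as not to see feedback that might reveal it. On that reading the procedure is coherent, and who holds the key is the kind of detail left to a full protocol. This reading is possible and cannot be excluded. It does not dispose of the point: the text says that allocation is provided and calls the code a group code, and a label shared within an arm would still sort participants into two sets.

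Several stronger conclusions that a reader might draw are not supported:

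- **That one remark would unmask the whole trial.** This needs a code shared by all 95 in an arm, which the protocol does not state. Under Training task both arms also receive feedback in the same form, and the rules differ by two steps of a 15-image sequence, so a casual remark need not be revealing.
- **That entry to the trial is biased.** Eligibility is settled before the allocation is requested.
- **That the lead researcher rates the Hamilton scale, or is the experimenter whose helpfulness is rated.** The protocol identifies neither.
- **That baseline mood is rated with the arm known.** The order is permitted, not specified. A BDI-II score of at least 14 is an inclusion criterion, so a BDI-II score must exist before screening is passed; the table's timings are approximate.
- **That participants' blinding fails.** Nothing in the document shows this.

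It is also fair to say that removal after randomisation is an analysis-population question in its own right, which would remain even with perfect masking. Knowledge of the allocation makes it worse because it allows removal to depend on the arm.

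**Conclusion.** The point holds in a limited form. As written, the person who receives the allocation and enters the group code is protected only by being out of the room, and that does not blind someone who holds the allocation. If the code is masked but shared within an arm, the protection is partial. If it is masked and unique to each participant, it is sound, but the protocol does not say so.

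The exposure is confined to removals after randomisation, where one criterion is the lead researcher's opinion, and to any outcome that person rates. The first can reach the primary analysis whoever completes the BDI-II. The second depends on an assumption about the Hamilton rater that the document neither confirms nor denies. The timing of baseline mood is a secondary gap.

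The size of any bias cannot be stated. The change is still worth making, because it improves on the stated procedure whether or not the code is masked, at almost no cost. It is not grounds for saying that the trial is unblinded.

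**What to change.** 1. The collaborator loads the allocation list into the task software before the study, keyed by a unique participant number. The lead researcher enters only that number and never receives a group or a group code.
2. Allocation for a participant is activated only after the baseline mood assessments at minute 50 of Table 1 are complete.
3. The Randomisation section states both rules in place of the present sentences on providing the allocation and entering the code. If the existing code is already opaque and unique to each participant, the section should say so; the timing rule is then the only change of procedure.

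The helpfulness rating can stay. A question asking participants, and any staff rater, to guess the allocation would test blinding more directly, but it is optional.

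The cost is a small software set-up task for the collaborator, with no extra visits. Under Trial status, one participant had been recruited when the article was submitted, so the change could have covered nearly the whole sample.
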